### Outcomes and others measures

#### Primary outcome measures

The **primary outcome measures relating to objective 1 **include the description of the implementation of preventive services according to the PAPPS criteria [6].

Screening for smoking status: if there is information on the consumption of tobacco over the last two years in members of the population who previously were non-smokers.

Screening for excessive alcohol consumption: if there is information on the consumption of alcohol over the last two years in members of the population who previously were not high consumers of alcohol.

Screening for obesity: if there have been measurements of height and weight or body mass index (BMI) over the last 4 years in members of the population who previously were non-obese.

Screening for hypertension: if there is information on systolic blood pressure (BPS) and diastolic blood pressure (BPD) during the last 4 years in members of the population aged between 16 and 40 years who previously did not have the diagnosis of hypertension; or over the past 2 years in members of the population older than 40 years who previously did not have the diagnosis of hypertension.

Screening for hypercholesterolemia: if there is information on total blood cholesterol corresponding to the following criteria of age and gender: 1 measurement in males between 16–35 years old; 1 measurement in females between 16–45 years old; 1 measurement every 5 years in males between 35–75 years old; 1 measurement every 5 years in females between 45–75 years old; 1 measurement if there has not been a previous measurement in those older than 75; all of these performed in population that previously did not have the diagnosis of hypercholesterolemia.

Anti-tetanus vaccination (ATV): if there is a registry of anti-tetanus vaccination over the previous 10 years.

Anti-influenza vaccination (AIV): if there is a registry of annual anti-influenza vaccination in those older than 59 years of age.

The **primary outcome measures relating to objective 2 **describes the clinical follow-up of the five health problems identified up to December 31^st ^2007 and evaluated up to December 31^st ^2008:

Evolution of tobacco consumption: quit smoking or remaining an ex-smoker.

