Evolution of excessive alcohol consumption: cessation of consumption or decrease below the definition of excessive consumption (28 alcohol units/week in males and 17 alcohol units/week in females, where 1 alcohol unit = 10 grams of alcohol).

Evolution of obesity: decrease in BMI to <30 kg/m^2 ^or change in the diagnosis to non-obese.

Evolution of hypertension: mean of the last 2 determinations of systolic BP/diastolic BP registered as being ≤ 130/80 mmHg in patients of high risk (diagnosed with diabetes, renal or cardiac insufficiency) and ≤ 140/90 mmHg in the rest of the population.

Evolution of hypercholesterolemia: last measurement of LDL cholesterol registered as being ≤ 100 mg/dL in high-risk patients (diagnosed with diabetes, ischaemic heart disease or cerebrovascular accident) and ≤ 130 mg/dL in the rest of the population.

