#### Other measures

We assess the following factors related to the outcome measures according to the levels of analysis:

Computerized PHCT: variables of structure and organization of the PHCT (number of GPs and nurses, presence of specialists), adherence to PAPPS, training centre for family doctors, ECR system and starting year, assigned population.

Health-care professionals (GPs, nurses): gender, age, specialty, years of employment in PC and in the PHCT, workload (mean number of visits/day), years of experience with ECR.

Subjects: gender, age, comorbidity according to the Adjusted Clinical Groups grouper [40,41], frequency of consultations (visits/year).

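### Objective 2 scores alcohol and obesity by crossing a cut-off, but the listed subject-level factors omit how far above the cut-off each case started

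*Protocol article*

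**What the plan says.** All references are to the protocol article.

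- **Alcohol (Primary outcome measures).** Success is "cessation of consumption or decrease below the definition of excessive consumption (28 alcohol units/week in males and 17 alcohol units/week in females"). The cut-off for success is, by the article's own wording, the one that defines the problem.
- **Obesity (same section).** There are two routes to success: "Evolution of obesity: decrease in BMI to <30" kg/m², or "change in the diagnosis to non-obese". The baseline definition of obesity is not stated; BMI of 30 or more is the natural reading.
- **Other outcomes (same section).** For hypertension the record rule is the "mean of the last 2 determinations of systolic BP/diastolic BP registered as being" at or below target. For hypercholesterolemia it is the "last measurement of LDL cholesterol registered as being" at or below target. No record rule is given for BMI or alcohol.
- **Time frame.** The section "describes the clinical follow-up of the five health problems identified up to December 31" 2007, with evaluation to the end of 2008. Study population requires one visit in 2006–2007 and a further one in 2008.
- **Factors (Other measures).** The patient-level list reads: "Subjects: gender, age, comorbidity according to the Adjusted Clinical Groups grouper [40,41], frequency of consultations (visits/year"). Qualifying BMI and qualifying intake are not in it.
- **Models (Statistical analyses).** Adjusted multilevel models are planned for objective 2 and adjusted ICCs for objective 3. They allow for other clinically relevant variables and for checked confounders, without naming any. A multilevel linear model is planned for continuous outcomes.

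**The concern.** When a case is defined by lying on one side of a cut-off and success by lying on the other, the chance of success depends strongly on the starting distance. Someone recorded at BMI 30.3 and later at 29.8 counts as controlled, although ordinary weighing error could produce that difference. Someone who starts at 36 needs a large true change.

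This would be harmless if objective 2 only reported an overall percentage. But the Design section also asks for the determinants of variability, and objective 3 is to publish variance components and ICCs for these outcomes. If teams or professionals differ in how many borderline cases they record, their success proportions differ with identical patient change. Those differences enter the random effects, the coefficients of team-level factors and the ICCs. With more than 850,000 subjects planned, the large sample does not remove such a difference; it estimates it precisely.

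**Working it through.** The plan states no figure on this point, so there is none to reproduce. The question is how much crossing noise alone can produce.

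**Inputs.** Cut-off of 30 kg/m² (Primary outcome measures). Everything else is assumed because the document gives no values: true BMI normal with mean m = 27 and SD s = 4.5; each recorded value equals the true value plus independent error with SD w = 0.5, 0.75 or 1.0; one value at entry and one at follow-up; no true change.

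**Formula.** Entry value B and follow-up value F are bivariate normal with mean m, variance s² + w² and correlation r = s²/(s² + w²). For w = 0.5, r = 20.25/20.50 = 0.988; for w = 1.0, r = 20.25/21.25 = 0.953. The quantity wanted is P(F < 30 | B ≥ 30), and the same within bands of B.

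| w | All entries ≥30 | Entry 30 to <32 | Entry ≥32 | Share of cases at 30 to <32 |
|---|---|---|---|---|
| 0.5 | 7.9% | 16.8% | 0.02% | 46.9% |
| 0.75 | 11.7% | 24.5% | 0.5% | 46.5% |
| 1.0 | 15.4% | 30.9% | 2.2% | 46.0% |

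Check of the first row: 0.469 × 16.75 + 0.531 × 0.02 = 7.9. With m = 26, s = 4.5 the overall figures are 8.9% to 17.4%; with m = 28, s = 5 they are 6.0% to 11.8%.

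**Gap between two teams, no true change in either.**

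- One team records every case at 30 or more; the other records nobody at 30 to <32. The gap is 7.9 − 0.0 = 7.9, 11.7 − 0.5 = 11.2 and 15.4 − 2.2 = 13.2 points.
- The second team instead records half of the cases at 30 to <32. For w = 0.5 its proportion is (0.5 × 0.469 × 16.75 + 0.531 × 0.02)/(0.5 × 0.469 + 0.531) = 5.1%. The same formula gives 7.8% and 10.7% for w = 0.75 and 1.0. The gaps are 2.7, 3.9 and 4.6 points.

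**ICC from labelling alone.** With teams split equally between two habits with success proportions p₁ and p₂, ICC = ((p₁ − p₂)/2)² / (p̄(1 − p̄)), where p̄ is their mean.

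- Extreme split, w = 0.5: (0.0785/2)²/(0.0394 × 0.9606) = 0.041. For w = 1.0: (0.1322/2)²/(0.0876 × 0.9124) = 0.055.
- Half-labelling split: (0.0272/2)²/(0.0651 × 0.9349) = 0.003 for w = 0.5 and (0.0463/2)²/(0.1306 × 0.8694) = 0.005 for w = 1.0.

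The planning ICC is 0.05, so the artefact ranges from negligible to as large as that value, depending on an unknown labelling contrast.

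**Alcohol.** The result is more sensitive to the assumptions. If 5% to 10% of people lie above the cut-off and a recorded intake has log-scale reliability 0.9 to 0.7, 31% to 61% fall below at the next record with no true change. With log-normal intake in men (median 10 units/week, log-SD 0.9) and a reporting CV of 10% to 40%, it is 10% to 35%. Only the direction is secure.

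**Why mean change helps.** In the BMI model the expected spurious fall is (1 − r)(B − m). At B = 30 it is 0.012 × 3 = 0.04 (w = 0.5) to 0.047 × 3 = 0.14 kg/m² (w = 1.0); at B = 35 it is 0.10 to 0.38 kg/m². It is small and does not pile up at the cut-off.

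**The case against.** Several points on the other side stand.

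- **Being below a threshold is a legitimate description of control.** Study objectives speaks of degree of control, and the LDL outcome also rests on one last value. This is not a contradiction or a numerical error, and the cut-offs are not in question.
- **A reader might infer that one record is enough.** The text does not say so. It is silent on which or how many BMI or alcohol records count, and a full protocol may settle it. The visit requirement only shows that a single later record could be all there is.
- **A reader might infer that starting severity will not be adjusted for.** That goes too far. Statistical analyses admits further clinically relevant variables and confounders. The qualifying value is unnamed, not excluded.
- **Obesity has a second route.** A change of diagnosis needs no BMI value, and the calculation does not model it. Nor does it model cases entered by a clinical diagnosis rather than one reading.
- **Teams may label alike.** Noise common to all teams shifts the overall level but creates no difference between them. The article acknowledges incomplete recording, but does not show that teams differ in the way assumed here.

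What survives is narrower. The factor list is stated, it leaves out the variable most directly tied to the chance of crossing, and two of the five primary outcomes of objective 2 depend on it.

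**Conclusion.** The point holds as a case-mix weakness. For alcohol and obesity, the proportion controlled, the team and professional effects and the ICCs will partly reflect how close to the cut-off the cases started, and the named subject-level factors do not capture this.

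The size cannot be derived from the document. Under the stated BMI assumptions, about 8% to 15% of cases cross with no true change, almost all of them from entry values of 30 to <32. A reader might infer from this that labelling habits alone separate teams by 10 points or more. That needs the extreme contrast in which one team records nobody in that band, and at within-person SD 0.5 even that gives only about 8 points. If the team records half of them, the gap is about 3 to 5 points.

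A reader might also infer that the outcome definitions must be replaced. The documents do not support that. Requiring a 5% fall still leaves 8.5% false success at within-person SD 1.0, and it would score a true fall from 30.5 to 29.2 (1.3/30.5 = 4.3%) as failure. Requiring two records would make success depend on how often a team records.

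**What to change.** 1. Keep the outcome definitions and cut-offs.
2. Under Other measures and Statistical analyses, name the last recorded BMI (obesity) or units/week (alcohol) up to 31 December 2007 as a subject-level covariate in the adjusted objective 2 models and the adjusted ICCs for these two outcomes. Show the unadjusted ICCs beside them, as already planned.
3. Report mean change in BMI and in units/week with the multilevel linear model already planned, next to the proportions controlled. The covariate does not alter the crude proportions, so the mean change is what lets a reader judge them.
4. A minimum-fall or confirmed-record definition is at most an optional sensitivity analysis.

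Cost: one covariate per model and one further continuous outcome for each of the two problems, using values that the threshold definitions already need. The downside is that subjects with a coded diagnosis but no recorded baseline value drop out of these adjusted models or need a missing-value category. Their number should be reported by team, since it may itself vary with recording practice.

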### Sources of information in Primary Care: the computerization of clinical records

Primary Care uses electronic clinical records (ECRs) to monitor health problems and to register preventive care services. Although information collection intends to be comprehensive, the ECR systems are different for each region.

Routinely-collected data have undisputed advantages in the study of CPV; they are available almost instantaneously and provide information on a large number of patients. The creation of registries or databases of health-care interest in PC was given a considerable boost with the computerization of clinical records. Spain, contrary to other countries [19-23], has little experience in the use of nation-wide databases containing electronic clinical records in PC. Recently, projects such as the BIFAP project in pharmacoepidemiological research [24] have been initiated in Spain.

However, there are certain difficulties in their use: 1) The data was originally collected for a function different from current research requirements; 2) ECR systems are different in each region, with different standards and computer programs; 3) The heterogeneous degree of implementation in PHCTs; and 4) The degree of exhaustivity of data recorded (for example, some activities are carried out but are not registered). Nevertheless, the potential of this type of registry has been confirmed by different European experiences mentioned earlier [25-27]. As such, the advantages associated to computerization of clinical records are beginning to be appreciated by the different regions and the richness of information provides enormous potential for the study of CPV in primary care.

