### Study objectives

The planned objectives in the present study are:

- To describe the variability in the performance of 7 preventive services (detection of smoking status and excessive alcohol consumption; screening for hypertension, obesity and hypercholesterolemia; anti-influenza and anti-tetanus immunization) in a population older than 16 years of age receiving attention in years 2006 or 2007 and to analyse factors related to their implementation.

- To analyse the evolution of 5 identified health problems (decrease in consumption or abstention from tobacco and alcohol and degree of control of hypertension, hypercholesterolemia and obesity) up to December 2008 in the population older than16 years of age attended by the reference PHCT at least once between 2006 and 2007 and followed up during 2008.

- Estimate the ICC, together with the within-cluster and between-cluster components of variance for each of the outcome measures of interest at the PC level.

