#### Quality control

Quality controls will be carried out in the 2 extractions of data comparing agreement between the central database and the original data of some centres as for: number of patient, visits and diagnoses as well as data of prevalence of certain diseases. It will also be checked if the population data is appropriate by comparing it with data from the census and other official sources. In the case of items related to clinical activities (for example blood pressure measurement), any register with missing values will be considered as not performed.

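### The obesity-control definition lets a changed diagnosis count as success even when the last recorded BMI is still 30 or more, because no rule says which source prevails

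*Protocol article*

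**What the plan says.** The outcomes for objective 2 are primary outcomes. The protocol article (Primary outcome measures) says that this set "describes the clinical follow-up of the five health problems identified up to December 31" 2007, with evaluation to the end of 2008. Study objectives names what they serve: "degree of control of hypertension, hypercholesterolemia and obesity".

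The obesity definition has two routes joined by a simple alternative:

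- a measured route: "Evolution of obesity: decrease in BMI to <30 kg/m"²;
- a diagnosis route: "or change in the diagnosis to non-obese".

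The diagnosis route carries no BMI condition. The article does not say which source decides when they disagree, and it does not limit the diagnosis route to patients without a BMI.

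The two neighbouring definitions rest on measurements only: "Evolution of hypertension: mean of the last 2 determinations of systolic BP/diastolic BP registered" at or below the stated limits, and "Evolution of hypercholesterolemia: last measurement of LDL cholesterol registered" at or below the stated limits.

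**The concern.** A definition of control should not be met by a patient whose own recorded measurement shows the condition is still present. The obesity definition allows this. A patient with a last BMI of 32 and an obesity entry changed to non-obese satisfies the second route and is a success.

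The study aims to explain variation between teams and professionals, and to publish ICCs and variance components for others to use in planning. Closing or editing a problem entry is a recording habit that could differ between professionals and teams. If it does, part of the variation reported as obesity control would be variation in record keeping, with no difference in weight behind it.

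**Working it through.** No figure in the article depends on this definition, so there is nothing to reproduce. The check has two parts: a reading of the wording, and an illustration of size on assumed rates.

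**Reading the definition.** Let A be BMI below 30 and B a diagnosis changed to non-obese. Success is A or B.

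| Last BMI in evaluation period | Diagnosis changed | Literal result |
|---|---|---|
| below 30 | either | success |
| 30 or more | no | not a success |
| 30 or more | yes | success (the conflict case) |
| none recorded | yes | success |
| none recorded | no | neither route met; handling not stated |

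The third row is the problem. Three places might have restricted it:

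- Study population requires a visit in 2008 but not a BMI at that visit.
- Quality control says that for clinical-activity items "any register with missing values will be considered as not performed". This concerns whether an activity was done, and it does not cancel the diagnosis route.
- Statistical analyses specifies models and adjustment, not outcome scoring.

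None of them restricts the row.

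**Effect on the proportion.** The article gives no rates, so the inputs are assumptions. Let p be the share of identified obese patients with a measured BMI below 30, and q the share of all identified obese patients who succeed on the diagnosis alone. The observed proportion is p + q and the relative rise is q/p.

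- p = 10%, q = 1%: 11% observed, relative rise 1/10 = 10%.
- p = 5%, q = 3%: 8% observed, relative rise 3/5 = 60%.

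A wider range uses c, the share of the remaining patients who are recoded, so that q = (1 − p)c. With p = 10%:

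- c = 2%: 0.10 + 0.90 × 0.02 = 11.8%; diagnosis-only successes are 1.8/11.8 = 15% of all successes.
- c = 5%: 14.5%; 4.5/14.5 = 31%.
- c = 10%: 19.0%; 9.0/19.0 = 47%.

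**Effect on the ICC.** Suppose true control is identical in all teams, half the teams recode and half do not, giving observed proportions b and a. With m = (a + b)/2, the ICC from recoding alone is ((b − a)/2)² / [m(1 − m)].

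- a = 10%, b = 11%: 0.005² / (0.105 × 0.895) = 0.0003.
- a = 5%, b = 8%: 0.015² / (0.065 × 0.935) = 0.004.
- a = 10%, c = 5% (b = 14.5%): 0.0225² / (0.1225 × 0.8775) = 0.005.
- a = 10%, c = 10% (b = 19%): 0.045² / (0.145 × 0.855) = 0.016.
- a = 10%, c = 20% (b = 28%): 0.09² / (0.19 × 0.81) = 0.053.

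The planning ICC (Sample size and randomisation) is 0.05. Only the last, extreme case reaches it. All these figures treat every diagnosis-only success as wrong. The conflict cases are a subset, so the misclassification that the wording certainly allows is smaller.

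**The case against.** **The conflict case is inferred.** The article never describes a patient with a high BMI and a closed diagnosis, and a condensed article may leave precedence rules to a fuller document. This limits how strongly the point can be put. It does not remove it, because the definition is stated and, applied as stated, it scores that patient as a success.

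**A diagnosis change need not be administrative.** It may reflect a clinician's judgement or a weight that was not entered, and the route may be meant for patients whose obesity was recorded without a BMI. This stands. A reader might infer that the outcome mostly measures record editing, but the document gives no evidence for that. It is also a reason not to discard diagnosis-only successes altogether: a BMI-only outcome would depend on which teams re-weigh their patients.

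**Unmeasured patients.** A reader might infer from Quality control that a patient with neither a BMI nor a diagnosis change is scored a failure. That sentence governs whether an activity was performed; it does not say how control is scored.

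**Record systems.** The background on information sources says "ECR systems are different in each region, with different standards and computer programs", which might suggest that regional differences in control are a software effect. Much of this is handled. Each region uses one system (Information source), analyses are also run by region (Statistical analyses), and the record system is a listed team-level factor (Other measures). Two gaps remain. In the global analysis the system coincides with Catalonia versus the other two regions, so adjustment cannot separate the two. And neither measure touches habits that differ between teams or professionals on the same system.

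**Size.** Every rate above is assumed, and the 60% figure pairs the least favourable values. This is correct, and it limits the verdict.

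**Conclusion.** The point holds in limited form. As worded, the obesity outcome scores as controlled a patient whose last recorded BMI is 30 or more if the diagnosis has been changed. The hypertension and LDL outcomes beside it have no such route.

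The frequency cannot be known from the document. If 5–10% succeed by measurement and 1–3% on the diagnosis alone, the proportion rises by 1–3 percentage points and the ICC from recoding is negligible to small (about 0.0003–0.004 with half the teams recoding). A distortion on the scale of the planning ICC would need half the teams to recode about 20% of uncontrolled patients, and nothing in the document suggests that. The point affects one of the five outcomes under objective 2. It merits correction because the misclassification follows from the stated rule and is easy to prevent, not because a large bias has been shown.

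**What to change.** Amend the obesity definition under Primary outcome measures:

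- Where a BMI is recorded in the evaluation period, score obesity on the last one (below 30 kg/m² or not). Using the last value matches the rule already used for LDL.
- Let a change of diagnosis to non-obese count only when no BMI is recorded in that period.
- Report how many successes rest on the diagnosis alone.
- As a sensitivity analysis, repeat the control proportion and the ICC among patients with a recorded BMI.

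The cost is a sentence or two in the definition, one extra table row and one repeated analysis. BMI and diagnosis are both already needed for the outcome as it stands, so nothing further need be extracted. The success proportion may be slightly lower. The subset with a BMI is selected by who gets re-weighed, which is why it belongs in a sensitivity analysis and not in the primary definition.
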